**Volunteer Instructions**

Subjects will be instructed not to wear any facial makeup or apply any skin care products or sunscreen on the face and neck on the day of the baseline, 4 and 8 week study visits. At the day of the 4 and 8 week visits will also be instructed to apply the study facial cream at least 2 hours prior to the study visits. They will also be instructed to discontinue using all of their current skin care products such as serums and moisturizers except the study product for the duration of the study. The study anti-aging cream (applied manually using their normal technique or using the prototype massage applicator) will be used at home twice per day for the 8 week duration of the study.

**Procedures**

1. Evaluation Procedures:

*Recruiting:*

- Potential volunteers will be contacted via a recruiting database
- Interested volunteers meeting the online screening criteria will be scheduled for a baseline visit.

*Pre-Study Instructions:*

The day of the baseline visit subjects will be instructed not to use apply any makeup, sunscreen, or moisturizer on their face and neck for at least 2 hours prior to the study visit.

B. Outline of Procedures:

| **Procedures** |  |  |  |
| --- | --- | --- | --- |
|  | Baseline | 4 Week | 8 Week |
| No facial skincare products including makeup, moisturizer, and sunscreen on face and neck at least 2 hours before the study visits | X |  |  |
| Informed consent, medical history, entrance criteria | X |  |  |
| 15 minute acclimation period | X | X | X |
| No skincare products (makeup, sunscreen) besides the study cream prior to the study visits (eye makeup permitted) |  | X | X |
| Confirm subject has used the study products at least 2 hours prior to the study visit (no sunscreen) |  | X | X |
| Esthetician Tolerance Assessment  Erythema Dryness  Peeling Edema | X | X | X |
| Subject Tolerance Assessment  Stinging Itching  Tingling Burning | X | X | X |
| Esthetician Efficacy Assessment  Face (forehead, cheek, lips, global face, sagging. Glabella lines, texture)  Neck (overall appearance, sagging, neckfolds, texture) | X | X | X |
| Photography  -Vectra | X | X | X |
| Volunteer Instruction distribution | X |  |  |
| Product Distribution/Return***** | D | D** | R |
| Subject randomized to treatment & trained | X |  |  |
| Subject Questionnaire |  | X | X |
| Subject compensation |  |  | X |

***D=dispense; R= Return**

**** only if additional product is needed**

C. Assessments:

*Clinical grading assessments:*

Clinical grading of efficacy parameters will be performed at baseline, 4 & 8 weeks. Subjects will be provided with a black headband to keep hair away from the face and instructed on proper headband placement. Full face and neck efficacy parameters will be assessed on each subject using the modified Griffiths’ 10-point scale recording to the following numerical definitions (half-point scores may be used as necessary to more accurately describe the skin condition):

0 = none (best possible condition)

1 to 3 = mild

4 to 6 = moderate

7 to 9 = severe (worst possible condition)

The following parameters to assess the **face** will be evaluated using the indicated scale anchors:

| Parameter | Location | 0 = | 9 = |
| --- | --- | --- | --- |
| Facial sagging (global) | Overall | None | Severe sagging |
| Texture | Overall | Even | Severely rough and uneven skin |
| Fine lines/wrinkles  Glabella lines | Forehead, cheek, lip, global face  Forehead | None    None | Numerous, deep wrinkles  Numerous, deep lines |

The following parameters to assess the **neck** will be evaluated using the indicated scale anchors:

| Parameter | Location | 0 = | 9 = |
| --- | --- | --- | --- |
| Sagging (global) | Overall | None | Severe sagging |
| Neck folds  Texture  Overall appearance | Overall  Overall  Overall | None    Even  Very healthy | Numerous, deep folds  Severely rough and uneven skin  Very unhealthy |

*Tolerance assessments:*

Tolerability evaluations will be performed at baseline, weeks 4 and 8. Local cutaneous tolerability will be evaluated by assessing the overall signs and symptoms of erythema, edema, dryness, and peeling and by the subject reporting the overall degree of burning, stinging, itching, and tingling.

For overall assessments of subjective irritation, subjects will report the degree of any parameters that they typically experience when using a product similar to the test material(s) at the baseline visit. At post-baseline time points, subjects will report the degree of any of these symptoms they have experienced since the previous time point.

The following static (without reference to any prior visits) scales and definitions will be used for overall tolerability evaluations (with half-point scores used as necessary to better describe the clinical condition):

Objective Irritation Parameters:

| Erythema | |
| --- | --- |
| 0 = None | No erythema of the treatment area |
| 1 = Mild | Slight, but definite redness of the treatment area |
| 2 = Moderate | Definite redness of the treatment area |
| 3 = Severe | Marked redness of the treatment area |

| Edema | |
| --- | --- |
| 0 = None | No edema/swelling of the treatment area |
| 1 = Mild | Slight, but definite edema of the treatment area |
| 2 = Moderate | Definite edema of the treatment area |
| 3 = Severe | Marked edema of the treatment area |

| Dryness | |
| --- | --- |
| 0 = None | No dryness of the treatment area |
| 1 = Mild | Slight, but definite dryness of the treatment area |
| 2 = Moderate | Definite dryness of the treatment area |
| 3 = Severe | Marked dryness of the treatment area |

| Peeling | |
| --- | --- |
| 0 = None | No peeling of the treatment area |
| 1 = Mild | Slight, but definite peeling of the treatment area |
| 2 = Moderate | Definite peeling of the treatment area |
| 3 = Severe | Marked peeling of the treatment area |

*Subjective Irritation Parameters*:

| Burning | |
| --- | --- |
| 0 = None | No burning of the treatment area |
| 1 = Mild | Slight burning sensation of the treatment area; not really bothersome |
| 2 = Moderate | Definite warm, burning of the treatment area that is somewhat bothersome |
| 3 = Severe | Hot burning sensation of the treatment area that causes definite discomfort and may interrupt daily activities and/or sleep |

| Stinging | |
| --- | --- |
| 0 = None | No stinging of the treatment area |
| 1 = Mild | Slight stinging sensation of the treatment area; not really bothersome |
| 2 = Moderate | Definite stinging of the treatment area that is somewhat bothersome |
| 3 = Severe | Marked stinging sensation of the treatment area that causes definite discomfort and may interrupt daily activities and/or sleep |

| Itching | |
| --- | --- |
| 0 = None | No itching of the treatment area |
| 1 = Mild | Slight itching sensation of the treatment area; not really bothersome |
| 2 = Moderate | Definite itching of the treatment area that is somewhat bothersome |
| 3 = Severe | Marked itching sensation of the treatment area that causes definite discomfort and may interrupt daily activities and/or sleep |

| Tingling | |
| --- | --- |
| 0 = None | No skin tingling sensation of the treatment area |
| 1 = Mild | Slight, but definite tingling sensation of the treatment area |
| 2 = Moderate | Definite tingling sensation of the treatment area that is somewhat bothersome |
| 3 = Severe | Marked tingling sensation of the treatment area that causes definite discomfort |

1. Imaging Procedures

Prior to photography procedures, clinic personnel will ensure that subjects have a clean face with no makeup as described in the study procedures. Subjects will remove any jewelry from the area(s) to be photographed and acclimatize for at least 15 minutes to ambient conditions within the clinic before any photographs are taken. Subjects will be provided with a black headband to keep hair away from the face and instructed on proper headband placement. Subjects will be provided with a black matte cloth that will be draped over the subjects’ clothing.

Images will be taken with the Vectra camera to capture volumetric images. Every day prior to taking photographs the camera will be calibrated. All photos will be taken with one frontal view at baseline, week 4, and week 8. Positioning of the subject’s posture is crucial to ensure proper volumetric measurements. The subject must sit in an erect, upright posture with a relaxed facial expression emphasizing that the teeth slightly touch with a relaxed jaw (no clenching). Alignment of the facial position at varying time points is also crucial to quantify volumetric data.

1. Self-Assessment Questionnaires:

Subjects will complete a self-assessment questionnaire at baseline, week 4 and week 8. Questionnaires will be provided by the Consumer Evaluation group.

1. Study Procedures:
   The study researchers will conduct the following procedures:

*The following sequence of procedures will be conducted:*

| **Prescreening:** | | |
| --- | --- | --- |
| *Sequence:* | *Procedure* | *Conducted by:* |
| 1 | Potential volunteers will be contacted via a recruiting database | Study Coordinator |
| 2 | Interested volunteers meeting the criteria via online qualification questionnaire will be scheduled for study visits | Study Coordinator /volunteer |
| **Baseline visit:** | | |
| *Sequence:* | *Procedure:* | *Conducted by:* |
|  | WIRB approved Study Consent and Photograph Release forms signed and the subject acclimatizes for 15 minutes | Subject |
|  | Medical history reviewed and updated, Inclusion/exclusion criteria checklist reviewed and verified, and subject number assigned | Blinded Study Esthetician |
|  | Subject completes online baseline questionnaire | Blinded Study Esthetician |
|  | Confirm the subject has no makeup, skin care products including moisturizer and sunscreen on the face and neck (eye makeup/eye products permitted) at least 2 hours prior to the study visit. | Blinded Study Esthetician |
|  | The following tolerance & clinical grading assessments are conducted:   - Objective/Subjective tolerance assessments - Clinical Grading:   - *Face:*     - Forehead- fine lines/wrinkles     - Cheeks- fine lines/wrinkles     - Lips – fine lines/wrinkles     - Global - fine lines/wrinkles     - Facial sagging (global)     - Texture     - Glabella lines   - *Neck:*     - Overall appearance     - Sagging     - Neck folds     - Texture | Blinded Study Esthetician |
|  | Photos: Vectra | Photographer |
|  | Identify areas that the subject will follow for changes in their skin via the aid of a mirror | Unblinded Study Personnel |
|  | The subject will be given the following:   - Study instructions - Randomized to a treatment group - Dispense Volunteer Instructions and study product | Unblinded Study Personnel |
|  | The subject will trained on how to use the study products (only device group) | Unblinded Study Personnel |
|  | The subject is instructed to use the study products according the Volunteer Instructions sheet. The instructions will be reviewed step by step with each subject | Unblinded Study Personnel |
|  | The subject is reminded to bring all study products to next study visit | Coordinator |
| ***Visits 2 & 3 (4 & 8 week ±2 days study visits):*** | | |
|  | The subject acclimates for 15 minutes | Blinded Study Esthetician |
|  | Review medical history and document adverse events and protocol deviation as indicated. Confirm the subject has no makeup or sunscreen on face and has used study products at least 2 hours before appointment | Blinded Study Esthetician |
|  | Confirm the subject has used the study products on the face and neck twice per day (morning & bedtime). | Blinded Study Esthetician |
|  | The following clinical grading & tolerance assessments are conducted:   - Objective/Subjective tolerance assessments - Clinical grading assessments:   - *Face:*     - Forehead- fine lines/wrinkles     - Cheeks- fine lines/wrinkles     - Lips – fine lines/wrinkles     - Global - fine lines/wrinkles     - Facial sagging (global)     - Texture     - Glabella lines   - *Neck:*     - Overall appearance     - Sagging     - Neck folds     - Texture | Blinded Study Esthetician |
|  | Photos: Vectra | Photographer |
|  | Questionnaire completed | Subject |
|  | Additional study anti-aging cream dispense, if needed (Visit 2 only) | Blinded Study Esthetician |
|  | The subject is reminded to bring all study products to next study visit. The date of the next study visit verified and confirmed (Visit 2 only) | Study Coordinator |
|  | Study product collected (Visit 3 only)  The subject is compensated for participation (Visit 3 only) | Blinded Study Esthetician |

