**Statistical Analysis**

The clinical grading scores and tolerance scores (subjective and objective) will be compared for both treatments and with their respective baselines: Anti-aging applicator + prototype cream and manual application of prototype cream at all the time points (week 4 and week 8).

For comparison with baseline of each treatment, the normality of the difference (from baseline) will be tested with Shapiro-Wilk test. The following statistical analyses will be performed for comparisons:

- Parametric Paired t-test in case of normality of differences
- Non-parametric Wilcoxon Signed Ranks test in the inverse case

For comparing both the treatments with each other, the normality of the difference (between treatments) will be tested with Shapiro-Wilk test. The following statistical analyses will be performed for comparisons:

- Parametric t-test in case of normality of differences
- Non-parametric Mann-Whitney test in the inverse case

For normality tests, the statistical significance level is set at p≤0.01. For all other statistical tests, the statistical significance level is set at p≤0.05.

Clinical significance is equal to or greater than a half point difference in clinical grading scores. Clinical significance will be addressed only when the data is statistically significant.

The self-assessment data will be analyzed by a consumer perception team.

Final Report

Following the completion of the study, a final report will be prepared. The report will detail the number of subjects who completed the study, any protocol deviations, adverse events, modifications, and a summary of the data.

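### For the four subjective symptoms, the paired tests against baseline contrast the study product with recalled usual products, so they do not measure change from the pre-treatment state

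*Protocol*

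**What the plan says.** Three statements in the protocol bear on this point.

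- **Baseline question** (section C, Assessments, under Tolerance assessments): "subjects will report the degree of any parameters that they typically experience when using a product similar to the test material(s".
- **Question at weeks 4 and 8** (same paragraph): "At post-baseline time points, subjects will report the degree of any of these symptoms they have experienced since the previous time point".
- **Analysis** (Statistical Analysis): "The clinical grading scores and tolerance scores (subjective and objective) will be compared for both treatments and with their respective baselines". The within-arm methods are "Parametric Paired t-test in case of normality of differences" and "Non-parametric Wilcoxon Signed Ranks test in the inverse case".

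The grades run from 0 to 3 with half points allowed, and the protocol describes them as follows: "The following static (without reference to any prior visits) scales and definitions will be used for overall tolerability evaluations". The Visit Summary, the Outline of Procedures and the Study Procedures table list the four symptoms at baseline but do not redefine the question. Nothing in the protocol collects a separate pre-treatment symptom score or exempts the subjective items from the comparison with baseline.

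**The concern.** A paired test against baseline is normally read as change from the state before treatment. Here the two halves of the pair answer different questions. The baseline half asks about other products and a habitual experience. The later half asks about the study product over roughly four weeks. A subject who usually feels mild stinging with creams, and then gets mild stinging from the study cream, has a change of zero. A subject who recalls more than the study cream causes appears to improve.

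Safety/tolerability is a named endpoint group. Both arms use the same cream, so a comparison between arms cannot reveal irritation that the cream causes equally in both. The within-arm comparison with baseline is the only planned test that could, and for these four symptoms its reference may already contain product-induced irritation.

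**Working it through.** **Number of tests affected.** 4 symptoms x 2 post-baseline visits x 2 arms = 16 paired tests.

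**What the difference estimates.** For one symptom in one arm, let T be the mean score on study product, R the mean recalled score for similar products, and P the mean score that subjects would have given for actual symptoms before treatment.

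- Change from the pre-treatment state: T - P.
- What the plan tests: T - R.
- Discrepancy: (T - R) - (T - P) = P - R.

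If R exceeds P, worsening is understated. If R exceeds T as well, the test points to improvement. If R is below P, the error runs the other way. The protocol gives none of T, R or P, so it has no figure to reproduce and the size cannot be calculated from it.

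**Illustration.** The planned procedure was simulated for one symptom in one arm.

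- From the protocol: Shapiro-Wilk at 0.01, then paired t-test or signed-rank test at 0.05; 42 completers.
- Assumed: two-sided tests; equal arms, 42 / 2 = 21; P = 0; a symptomatic subject scores 0.5, 1 or 2 with probability 0.4, 0.4, 0.2; recall and on-treatment scores independent; signed-rank p-values by normal approximation with zero differences dropped; 3,000 runs.

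The mean score of a symptomatic subject is 0.4 x 0.5 + 0.4 x 1 + 0.2 x 2 = 1.0, so the expected difference is simply (share symptomatic on treatment) - (share recalling a symptom).

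Chance of a significant worsening:

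| Share recalling a symptom at baseline | 30% symptomatic on treatment | 40% | 50% |
| --- | --- | --- | --- |
| 0% | 82% | 97% | 99.7% |
| 5% | 49% | 73% | 87% |
| 10% | 30% | 52% | 71% |
| 20% | 8% | 24% | 41% |
| 30% | 2% | 8% | 19% |
| 40% | 1% | 3% | 8% |

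With 40% symptomatic and 60% recall, the expected difference is 0.4 - 0.6 = -0.2, and 17% of simulated trials show a significant improvement although, by assumption, treatment caused every symptom.

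**Check on the first row.** With no recall, every non-zero difference is positive, and the approximate signed-rank test generally reaches 0.05 once 5 of 21 subjects have a symptom. The binomial probability of 5 or more out of 21 is 80.2%, 96.3% and 99.6% at 30%, 40% and 50%, close to the simulated values. An exact signed-rank test would need 6, because 2 x 0.5^5 = 0.0625 but 2 x 0.5^6 = 0.031. The probability of 6 or more at 40% is 90.4%. The starting level therefore depends somewhat on the version of the test.

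**The case against.** The strongest reply is that the baseline question may be deliberate. Subjects stop their own moisturizers and serums only at baseline, with no washout beyond about two hours without product, so their pre-study state is not product-free. Asking what a similar cream usually does matches the later question in kind: usual cream against study cream. This reading is possible, but the protocol never states it. It treats the score as an ordinary baseline, in the same sentence and with the same tests as the objective signs. If the reading is right, the contrast still needs that label.

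A reader might go further and infer that the safety conclusion is definitely biased toward good tolerability. The documents do not support that:

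- The direction depends on recalled symptoms exceeding actual pre-treatment symptoms, and neither rate is given. The exclusions for known allergy to facial products, chronic facial skin problems and chemically hypersensitive skin may keep recall low.
- The protocol states no rule that turns zero change into a finding of no irritation. The absolute scores are collected, so mild stinging remains visible as a 1.
- The baseline question precedes randomization, so a between-arm comparison of raw week-4 or week-8 scores is not biased by it.
- Adverse events are sought at every visit and assessed for relatedness.

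These points limit the consequence. They do not make the paired difference a change from the pre-treatment state, and the between-arm test still cannot see what the shared cream does in both arms.

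A reader might also infer that the objective signs (erythema, edema, dryness, peeling) are free of any such difference because they are graded the same way throughout. The scale is the same, but the conditions are not: study cream is applied before the week-4 and week-8 visits, while no product is applied before baseline. This point makes no claim that their baseline comparison is sound.

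**Conclusion.** The point holds as a mismatch between how the baseline is defined and how it is analysed, confined to burning, stinging, itching and tingling. All 16 within-arm tests on these items contrast study product with recalled usual product. They can mask irritation, or suggest improvement, when recall exceeds true pre-treatment symptoms.

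The count and the identity P - R follow from the protocol's own definitions. The simulated percentages rest on assumed symptom rates, severities and nil pre-treatment symptoms. They show that even modest recall could matter with about 21 subjects per arm, and should not be read as this trial's expected loss. The matter should be corrected, because these are the only planned tests able to show irritation common to both arms.

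**What to change.** In Statistical Analysis, remove the paired baseline tests for the four subjective items as evidence of tolerability. Alternatively, keep them as descriptive only, explicitly labelled as study product versus recalled usual product.

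Base the subjective tolerability conclusion on the absolute post-baseline scores in each arm: number and percent at each severity per visit, and each subject's worst post-baseline score. Add the between-arm comparison, with a note that it cannot show effects of the shared cream.

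If baseline data are still to be collected, also ask about current or recent symptoms over the same recall window as the later visits, and keep the similar-product question as background. If they have already been collected, no pre-treatment symptom score can be recovered and the report should say so.

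The cost is a change of analysis wording and the loss of a formal within-arm p-value for these items. The added baseline question, where still possible, is the only change to data collection.

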| **Visit Summary** | *Baseline (Visit 1):*   - 15 minute acclimation period - Study & photograph consent forms signed - Medical History reviewed - Assign study number to the subject - The examiner blinded to the application method will conduct the following:   - Tolerance (0 – 3 point scale):     - Objective tolerance: erythema, edema, dryness and peeling     - Subjective tolerance: burning, stinging, itching and tingling   - Clinical grading assessments on the face and neck (0-9 point scale):     - Face:       - forehead wrinkles       - cheek wrinkles       - lip area wrinkles       - global facial wrinkles       - facial sagging       - glabella lines       - texture     - Neck:       - overall appearance       - sagging       - neck folds       - texture - Photos prior to product use: Vectra - Study personnel not blinded to the application method will randomize the subject to a treatment group - Study personnel not blinded to the application method will train the subject on product use:   - Have subjects examine their face and neck in a mirror prior to product use with study personnel pointing out areas to follow for the duration of the study; fine lines and wrinkles, sagging, texture, neck folds, glabella lines, overall appearance, etc.   - For subjects randomized to the *manual application groups*:     - No instructions on how to or how long or how much facial cream to apply the face and neck will be given. Subjects will be instructed to apply the study cream using the amount of cream and technique of application they normally use at home when applying a facial cream     - Subject applies the study cream to the face and neck using the amount of cream and technique they normally use at home to apply facial creams     - Subjects will be instructed to apply the study cream twice per day (morning and bedtime)   - For subjects randomized to the prototype device group:     - Subjects will be trained on how to use prototype device     - The study personnel will explain and demonstrated to the subjects how much cream to use with the anti-aging applicator and how to apply the cream to the treatment zones (refer to Volunteer Instructions)     - Subjects applies the prototype study cream to each treatment zone (forehead, cheeks/mouth and neck/jawline) for a total of 2 minutes and 15 seconds using the prototype device /prototype cream for the following times per treatment zone:       - Zone 1: forehead - 30 seconds       - Zone 2: cheeks and mouth area - 1 minute       - Zone 3: neck and jawline – 45 seconds     - Discontinue all current serum, moisturizer, and/or any other skincare products     - Subjects will be instructed to use the study products twice per day (morning and bedtime) - Remind subjects to bring all study products to next study visit - Instruct subjects to discontinue using their current serum, moisturizer, and/or any other skin care products and replace with study products - A sunscreen SPF 30 will be given to the subjects with instructions to apply the sunscreen every morning and to reapply throughout the day as needed   *Visit 2 & 3 [Visit 2[4 weeks (28 days ±2 days) post baseline], Visit 3 [8 weeks (56 days ±2 days) post baseline]*   - 15 minute acclimation period - Review medical history and discuss product use - Document adverse events and protocol deviation as indicated - Confirm subject has applied the study products per application method at least 2 hours prior to the study visit. - Confirm subject has no makeup, skin care products (eye products/eye makeup permitted) including sunscreen on the face and neck the morning of the study visit (besides study cream) - The examiner blinded to the application method will conduct the following:   - Tolerance (0 – 3 point scale):     - Objective tolerance: erythema, edema, dryness and peeling     - Subjective tolerance: burning, stinging, itching and tingling   - Clinical grading assessments on the face and neck (0-9 point scale):     - Face:       - forehead wrinkles       - cheek wrinkles       - lip area wrinkles       - overall facial wrinkles       - facial sagging       - glabella lines       - texture     - Neck:       - overall appearance       - sagging       - neck folds       - texture - Photos prior to product use: Vectra - Subject completes a self-assessment questionnaire - Additional product dispensed if needed (Visit 2 only)   Study products collected and subject compensated for participation (Visit 3 only) |

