**Protocol for the day of each study visit:**

- Morning of visits: Cleanse your face using your normal cleanser and cleansing method (approximately same time each morning)
- Apply the study facial cream approximately 2 hours prior to your study visit
- Apply the study sunscreen to the face (**only** for afternoon appointments)
- Afternoon Study visits**: 2 hours before your appointment** remove your facial makeup (do not need to remove your eye makeup). Apply the study facial cream approximately 2 hours prior to your study visit. **Do not** apply makeup or sunscreen to the face after use of the study cream.
- Please bring all study products to **all** your study visits

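### Blinding of the week 4 and week 8 clinical grades is not protected: the blinded grader is also given the product-use, adverse-event, deviation and dispensing tasks

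*Protocol*

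**What the plan says.** The Visit Summary in the Overview sets the standard for baseline and for visits 2 and 3: "The examiner blinded to the application method will conduct the following", followed by the tolerance and clinical grading lists. At baseline the Study Procedures table keeps to it. The Blinded Study Esthetician grades first, and Unblinded Study Personnel then randomize, dispense and train.

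For visits 2 and 3 the same table gives these steps to the Blinded Study Esthetician, in this order:

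- "Review medical history and document adverse events and protocol deviation as indicated", in one row with the makeup and sunscreen check and the 2-hour product-use check;
- "Confirm the subject has used the study products on the face and neck twice per day (morning & bedtime";
- tolerance and clinical grading;
- after photographs and questionnaire, "Additional study anti-aging cream dispense, if needed (Visit 2 only";
- last, "Study product collected (Visit 3 only".

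Before the grading at these visits the Visit Summary lists "Review medical history and discuss product use" and "Confirm subject has applied the study products per application method at least 2 hours prior to the study visit". It names no role for either line.

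Both sets of Volunteer Instructions say "Please bring all study products to" all visits. The device arm receives an applicator, handle, charger and cream; the manual arm receives no device. Under Supplies needed, cream is planned at 3 jars per device subject and 2 per manual subject.

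**The concern.** The treatment cannot be hidden from subjects, so the grader's blind is the main safeguard for the between-arm comparison of clinical grades. Those grades are subjective scores from 0 to 9, with half points allowed, and the Statistical Analysis section compares them between arms at weeks 4 and 8. A grader who learns the arm before scoring can shift the very contrast the trial is run to measure, and no later analysis can remove that shift.

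The protocol separates blinded from unblinded staff at baseline but not at the two visits where there is a treatment effect to grade. No Unblinded Study Personnel are listed for visits 2 and 3. The conversations and product handling most likely to reveal the arm fall to the one person who must not know it.

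**Working it through.** **Which tasks can reveal the arm, and when.** The Study Procedures table is introduced as a sequence, so row order matters.

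| Task at visits 2 and 3 | Assigned to | Position | Can it reach a grade? |
|---|---|---|---|
| Adverse-event and deviation review | Blinded Study Esthetician | Before grading | Yes, weeks 4 and 8: a device-related event or deviation identifies the arm |
| 2-hour use check | Blinded Study Esthetician | Before grading | Yes, weeks 4 and 8, if asked as the Visit Summary words it |
| Twice-daily use check | Blinded Study Esthetician | Before grading | Possibly: it asks about area and frequency, which the arms share |
| Extra cream, visit 2, if needed | Blinded Study Esthetician | After week 4 grading | Week 8 only |
| Product collection, visit 3 | Blinded Study Esthetician | After week 8 grading | No, for that subject |

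The Visit Summary and the table describe the same 2-hour check. Only the Visit Summary ties it to application method; only the table says who does it. Read together, the grader performs a check that cannot be completed as worded without knowing the method.

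**Jar supply.** 23 × 3 + 23 × 2 = 69 + 46 = 115, which matches the stated 115 jars. The arm difference in planned cream is therefore deliberate. The protocol does not say how many jars go out at baseline, so whether a visit 2 refill points to one arm is an inference.

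**Which scores are exposed.** The week 4 and week 8 clinical grades and objective tolerance scores. Baseline grades precede randomization, the photographer takes the Vectra images, and subjects complete the questionnaires.

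**Size, as illustration only.** The protocol has no figure to reproduce here. From the protocol: 42 completers, significance at p ≤ 0.05, clinical threshold 0.5 point. Assumed: 1:1 allocation (21 per arm), two-sided test, SD of 0.5, 0.75 or 1.0, no true effect, and a bias b of 0.1 or 0.25 point applied in full to one arm's mean.

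Standard error of the difference: SE = SD × √(2/21), giving 0.154, 0.231 and 0.309. With 40 degrees of freedom the critical t is 2.021, so the smallest significant difference is about 2.021 × SE = 0.31, 0.47 and 0.62 point. The rejection probability is P(|T| > 2.021), with T noncentral t, 40 degrees of freedom and noncentrality b/SE. The second rate also requires an observed difference of at least 0.5 in absolute value; it averages the normal probability of exceeding max(0.5, 2.021 × s × √(2/21)) over the sampling distribution of the pooled SD s.

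| Bias b | SD | b/SE | p ≤ 0.05 | p ≤ 0.05 and difference ≥ 0.5 |
|---|---|---|---|---|
| 0.1 | 0.5 | 0.65 | 9.7% | 0.5% |
| 0.1 | 0.75 | 0.43 | 7.1% | 4% |
| 0.1 | 1.0 | 0.32 | 6.2% | 6% |
| 0.25 | 0.5 | 1.62 | 35% | 5% |
| 0.25 | 0.75 | 1.08 | 18% | 13% |
| 0.25 | 1.0 | 0.81 | 12% | 12% |

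With no bias the first rate is 5%. The second, from the same formula with b = 0, is about 0.1%, 2.9% and 4.9% at the three SDs, so 5% is not its reference value.

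**The case against.** The best defence is that no row obliges the grader to see the device or ask about the method before scoring. The twice-daily check can be answered in either arm without naming the method. The wording by application method stands on a Visit Summary line with no role, and the table's version of that check omits it. Products come to the visit, but the protocol does not say where they are kept until collection. Dispensing is conditional, follows the week 4 grading, and hands over the same cream in both arms.

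All of this is fair, and it limits the conclusion. A reader might infer that the blind is broken for every efficacy score; the protocol does not support that. Imaging, questionnaires and baseline grades are outside the problem, and disclosure is likely rather than certain. A reader might also count visit 3 collection as a cause of bias, but it follows that subject's last grading.

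The defence does not answer the adverse-event and deviation review or the use checks. These put the grader in conversation about treatment directly before scoring, at both post-baseline visits, with no instruction to subjects to withhold their method and none to keep products out of sight.

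**Conclusion.** The point holds in limited form. The protocol promises a grader blinded to application method, then assigns that grader tasks at visits 2 and 3 that are likely to reveal it. The blind on the week 4 and week 8 clinical grades and objective tolerance scores is not protected.

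This rests on the role assignments and their order, not on the arithmetic. The illustration shows that a modest bias could matter: at p ≤ 0.05 the false-positive rate per test is about 6–10% for 0.1 point and 12–35% for 0.25 point. With the half-point threshold added it is about 0.5–6% and 5–13%. The 35% therefore applies to bare statistical significance at the smallest assumed SD. Bias, SD and allocation are assumptions, and the full-shift model treats every subject as unmasked, so partial unmasking would give less.

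It should be corrected before the trial starts, because the change is small and the bias could not be removed afterwards.

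**What to change.** In the Study Procedures table for visits 2 and 3:

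- Move the product-use checks, the adverse-event and deviation review, and cream dispensing to the Unblinded Study Personnel or the Study Coordinator, both already named in the table. Move product collection too, for consistency.
- Split the combined row, so that before grading the esthetician confirms only that no makeup or sunscreen is present.
- Have subjects hand in their products to the unblinded person at check-in, out of the grader's sight.

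Amend the Visit Summary to match, naming the role for the discussion of product use and for the 2-hour check. Add a line to both sets of Volunteer Instructions asking subjects not to mention their application method to the grader.

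The cost is staffing. An unblinded staff member or the coordinator must be present at both visits, whereas the table now lists no unblinded staff at either and the coordinator at visit 2 only. No extra assessor or visit is needed.
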